### Intervention and resuscitation scenarios

Each team will comprise six participants: (1) a team leader (fellow in pediatric emergency medicine), (2) a physician (resident in pediatrics) undertaking the primary/secondary surveys and performing the procedures, (3) a dedicated trained assistant for airway management, (4) a dedicated trained assistant for chest compressions, (5) a nurse for vascular access and drug preparation/administration, and (6) a scribe (second nurse) to document events and actions in a chronological fashion (either with the app or conventional methods). As PALS instructors and senior physicians, the study investigators will not interfere in the conduct of the CPR (except in the case of a significant deviation from the algorithm that must be followed to achieve ROSC; which will then be regarded as an error). Among them, a study investigator will play the role of on-call hospital specialists and radiologists, if needed. A second study investigator will operate the simulator and a third will freeze the situation at certain defined timepoints and provide the scripted questions.

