On the day of participation, each subject will complete an anonymous survey about basic demographic information, professional length of medical training, PALS and ATLS training, and simulation and computer experience. After random allocation, each team will receive: (1) a standardized 15-min training session on how to use the app, (2) a presentation of the simulation manikin’s characteristics, and (3) the topics of three assessment questionnaires (see below), but to prevent unblinding, not the queries themselves. The teams will then be asked to consecutively perform two 20-min highly realistic, scripted CPR scenarios on a high-fidelity WiFi manikin (Laerdal SimBaby, Laerdal Medical, Stavanger, Norway). High levels of realism are known to immerse participants in the simulated experience and prevent confounding variables that might potentially affect the way they perform [30]. Within each scenario, three separate “freeze” periods will occur at random points in time to assess the shared and complementary SA of each team member individually regarding the CPR in progress. During freezes, the entire team will have to turn away from the patient, monitors and app to “blank out” the simulator and avoid any cognitive help from the simulated environment that could otherwise bias the respondent’s answers to the questionnaires. The scenarios will be standardized to strictly follow the 2018 AHA pediatric ventricular fibrillation algorithms [5] (Fig. 5) and the 2018 ATLS guidelines [40]. They will be extensively tested before the trial to achieve optimum functioning on the day of participation and performed on the same high-fidelity manikin already primed with vital signs appropriate for the scenarios. Both scenarios will be completed in the same order and the procedure will be standardized across all teams to follow the same chronological progression and range of difficulty in order to ensure that each participant is exposed to exactly the same case, with similar challenges in technical and non-technical skills. The uniform delivery of the scenarios throughout the entire study will minimize confounders. Study investigators will allow progression through the scenarios only once predefined milestones have been reached, irrespective of error occurrence or the time taken to achieve them.

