#### Time to critical life-saving maneuvers

Team effectiveness (domain) will also be measured on video reviewing (specific measurement) as the time spent in seconds by the team to achieve the pre-designed goals set out by the AHA for the PALS course and the American College of Surgeons for the ATLS course [10, 51, 52]. They will comprise the elapsed time in seconds between the end of the clinical statement by the study investigator to (1) ventricular tachycardia or hypotensive shock recognition; (2) initiation of chest compression; (3) time to each defibrillation attempt; (4) time to administration of intravenous drugs, volume expansion with 0.9% sodium chloride or blood transfusion; and (5) time interval between defibrillation attempts (metrics). If not achieved within the 40-min scenario, this will be considered as a lack of goal completion. It should be noted that for the trauma scenario, we decided not to use the modified non-technical skills scale for trauma (T-NOTECHS). This decision is based on the serious risk of assessment bias with this instrument, as emphasized by the consensus-based standards for the selection of health measurement instruments (COSMIN) [50]. Mean times per goals will be aggregated to compare both study arms (method of aggregation). The time frame of interest for this endpoint is over the duration of the whole CPR scenario.

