### Power and sample size calculation

A previous study found a 23.5% SA improvement in intensive care unit nurses exposed to an integrated information display compared to a traditional display exposure [54]. In this trial, the sample size was calculated to provide 90% power at a two-sided alpha level of 5% in detecting a relative difference of at least 25% SA improvement between intervention groups, with an assumed standard deviation (SD) set at 0.2. This SD is based on and conservatively about twice as much as that observed by Koch et al. [54]. The required sample size is 14 participants per study arm. To prevent a potential loss of power due to misspecification of assumptions, 18 participants (= 3 teams of 6 people per team) should be recruited per randomized group. To take into account the cluster randomized trial design, this sample size was inflated using a variation inflation factor of 1.25 (= 1 + 0.05(6–1); 0.05 being the intraclass correlation coefficient). The total sample size (i.e., 45 participants) was finally rounded up to 48 participants to obtain 8 teams of 6 participants per team.

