Kaplan–Meier curves for the time elapsed between the end of the clinical statement by the study investigator and timed secondary outcomes will be compared using the log-rank (Mantel-Cox) test including a cluster term to account for the cluster randomized design. Wrong defibrillation or drug doses will be measured as a deviation from the amount of energy delivered in Joules or drug doses in milliliters compared to 2018 AHA PALS cardiac arrest algorithm, respectively. Use of epinephrine 0.1 mL/kg (0.1 mg/ml concentration) and amiodarone 5 mg/kg (150 mg/3 mL concentration) are expected for the first scenario. We define an emergency medication dose administration error as a deviation from the correct weight dose of more than 10% [55]. Moreover, defibrillations (in Joules) and the number of shocks will be also measured during the first scenario. Defibrillation doses of 2 J per kg for the first attempt and 4 J per kg for the subsequent second, third and fourth attempts are expected [5]. A GEE model with a Poisson link will be used to assess the relationship between absolute errors in defibrillation and drug doses expressed as categorical variables. Wrong defibrillation mode will be also measured. Absolute deviations will be analyzed. The mean (SD) difference obtained with each intervention method will be reported with a 95% CI. Univariable linear GEE with 95% CI will be performed to assess whether time to initiation of chest compression, defibrillation attempts, and drug delivery are associated with prior resuscitation experience as a clinician in real-life and simulated environments. Similar analyses will be carried out for errors in fluid resuscitation volumes (in milliliters) and blood transfusion during the second scenario. An initial 20 mL/kg bolus of isotonic crystalloid followed by 10–20 mL/kg of packed red blood cells and 10–20 mL/kg of fresh frozen plasma and platelets are expected [40].

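### The GEE planned for team times on prior experience does not suit goals timed once per team: eight team rows give too narrow a CI, and copied member rows would shrink the slope

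*Protocol article*

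**What the plan says.** The experience analysis is described in one sentence of Statistical analyses. It opens "Univariable linear GEE with 95% CI will be performed to assess whether time to initiation of chest compression", adds defibrillation attempts and drug delivery, and asks whether these times "are associated with prior resuscitation experience as a clinician in real-life and simulated environments". The model is therefore a linear GEE with one covariate and no arm term.

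Three other places fix the structure of the data:

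- **Outcome.** Time to critical life-saving maneuvers defines the measure as "the time spent in seconds by the team to achieve the pre-designed goals".
- **Covariate.** Intervention and resuscitation scenarios says that "each subject will complete an anonymous survey about basic demographic information", and lists training and simulation experience among the items.
- **Size.** The same section says "Each team will comprise six participants", in mixed roles (fellow, resident, two assistants, two nurses). Power and sample size calculation gives a total "finally rounded up to 48 participants to obtain 8 teams of 6 participants per team".

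The article does not say whether a row is a member or a team, whose experience enters, or which working correlation is used.

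**The concern.** The outcome exists once per team and the covariate exists six times per team. A GEE clustered on team can be fitted in two ways. Either the team time is copied to each member, or each team contributes one row per timed event with a single experience value.

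For repeated shocks or several drugs, the second layout still leaves several times per team, and a clustered model is reasonable. For a goal reached once, such as the start of chest compressions, it leaves eight clusters of one row, and the sandwich variance has very little to work with.

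What is at stake is how the result is read. With member rows, a slope close to zero could be taken to mean that experience does not matter, when its size comes from the data layout. With team rows, a chance association could be reported with an interval that is much too narrow.

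**Working it through.** **The plan's own figure.** The sample size is set for "90% power at a two-sided alpha level of 5% in detecting a relative difference of at least 25% SA improvement", "with an assumed standard deviation (SD) set at 0.2". Reading 25% as 0.25 on the scale of the SD gives 14 per arm (power 0.911 at 14). The plan raises this to 18; the design effect is 1 + 0.05 × 5 = 1.25; 2 × 18 × 1.25 = 45, rounded up to 48 = 8 × 6. The figure reproduces. It bears on this point only through the structure of 8 teams of 6.

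**Layout A: team time copied to six member rows.** Let b be the slope of team time on team-mean experience, SSB and SSW the between-team and within-team sums of squares of experience, and SST their sum. The time is constant within a team, so the within-team cross-product is exactly zero.

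- *Independence.* Slope = b × SSB/SST. If experience is unrelated among team members, the expected share is 7/(7 + 40) = 7/47 = 0.149. With an assumed within-team correlation of experience of 0.05, it is 7(0.30 + 0.95)/[7(0.30 + 0.95) + 40 × 0.95] = 8.75/46.75 = 0.19. With 0.30, it is 7(1.8 + 0.7)/[7(1.8 + 0.7) + 40 × 0.7] = 17.5/45.5 = 0.38. Simulated mean slopes against a true −5 were about −0.7, −0.9 to −1.0 and −2.0. With strong role differences they were −0.3 to −0.4.
- *Exchangeable.* The between-team part is weighted by w = (1 − ρ)/(1 + 5ρ). In the simulations ρ was estimated at about 0.975, so w ≈ 0.0254/5.873 = 0.0043. The slope is then b × 7w/(7w + 40) = b × 0.0303/40.03 ≈ 0.0008b, which is −0.004 for b = −5. The simulations gave −0.002 to −0.016.
- *Null.* In both cases the slope is b times a positive factor, so it is zero exactly when b is zero. In 200 simulated trials the team-level, independence and exchangeable slopes had the same sign every time.

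A second setting assumed a team-mean effect of 1.5 residual SD per SD. The median slopes were 3.7 (team level), about 0.50 (independence) and 0.0025 (exchangeable). When experience had no effect, default robust inference rejected in 9–17% of trials, depending on the working correlation and on how alike members' experience was.

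**Layout B: one row per team.** There is no dilution. Against a true −5, the mean slope was −4.7 to −5.1 on the team mean when the mean drives the time, and −4.9 to −5.2 on the leader's experience when the leader does. Inference is the weak point. With eight one-row clusters, the default robust variance uses raw squared residuals, which are too small on average because two parameters are fitted to 8 points, and it is referred to a normal distribution. Simulated rejection of a true null at nominal 5% was 20–23%. Ordinary regression with t-based intervals (8 − 2 = 6 df) rejected about 5%.

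**Arm.** With an assumed arm effect of −10, the mean team-level slope was −5.01 without arm and −5.09 with it, so leaving arm out neither biases nor dilutes it. Adding arm cut the SD of the slope from 6.9 to 3.8 (team mean) and from 2.8 to 1.5 (leader). With an arm effect of 1.5 SD, power rose from 66% to 76%. With no arm effect, adding arm cost 7–9 points of power.

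**The case against.** The strongest reply is that member rows are never stated. The plan also uses linear GEE for the RTLE and TEAM sum scores, which rate the leader and the team, so GEE in this article does not imply one row per member. Repeated shocks and several drugs give several times per team, for which a team-clustered GEE is a sound choice. Row unit, covariate coding and working correlation are details that a condensed article may leave to an analysis plan. All of this stands, and their absence is not the point made here.

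A reader might go further and infer that the slope will be diluted or forced to zero, that the model therefore cannot test for an association, and that leaving out arm is part of the cause. The documents do not support this. The dilution depends on a layout that the article does not state. Even under that layout the null of no association is preserved. Arm plays no part in the dilution; a univariable model estimates a crude association, and under randomisation that is not biased on average by leaving arm out.

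What the reply does not answer is the goal with one time per team. There the natural defence, one row per team, leads straight to the inflated error rate of default GEE inference on eight clusters. That concerns a method the article does name.

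**Conclusion.** The point holds in conditional form. For goals timed once per team, the stated linear GEE is a poor choice under either layout. Member rows shrink the reported slope to about 15% under independence (8% to 40% over the assumptions tried) or to effectively zero under exchangeable correlation. Team rows give the right slope but about 20% false rejection with default robust inference.

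The percentages rest on normally distributed experience and times, on the assumed effect sizes and within-team correlations shown above, and on software defaults without a small-sample correction. A correction adopted in an analysis plan would ease the second problem.

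The matter is minor. It concerns a secondary association analysis and touches neither the SAGAT comparison nor any between-arm test. Even the correct analysis is imprecise with 8 teams: the simulated SD of the team-mean slope was about 3.2 around a true value of 5 when experience was unrelated within teams.

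**What to change.** - **Goals with one time per team** (for example chest compression): use one row per team and ordinary linear regression with t-based 95% CIs in place of the GEE.
- **Covariate:** name one team-level experience measure in advance, either the leader's experience or the team mean. The choice matters. When the leader's experience drove the time, the SD of the slope was 1.5 using the leader's value and 5.8 using the team mean.
- **Repeated defibrillation attempts or drugs:** keep a team-clustered model with the same team-level covariate, and add a small-sample correction, such as a bias-corrected sandwich variance with a t reference.
- **Arm:** optional, for precision. Decide before the data are seen. It takes one degree of freedom (6 to 5) and costs about 7–9 points of power if the tool has no effect on the times.

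The cost is a change of wording and simpler code. No extra participants or measurements are needed, but survey responses must be linkable to team and, if the leader's experience is used, to role.

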### Dissemination policy

Final results of the trial will be reported in accordance with the Consolidated Standards of Reporting Trials of Electronic and Mobile Health Applications and Online TeleHealth (CONSORT-EHEALTH) [56] guidelines and the Reporting Guidelines for Health Care Simulation Research [57]. It is our intention to present these at scientific congresses and to publish the results in an international peer-reviewed journal, irrespective of the magnitude or direction of effect. The investigators of the research team will be named coauthors on all future related publications.

## Discussion

Pediatric CA is a high-risk low-frequency event associated with death or severe neurological sequelae in survivors. Recent studies show that p-IHCA affects 7100 to 8300 children per year in the USA [58], of which 14% occur in PEDs [59]. By contrast, p-OHCA accounts for a further 7037 children brought to United States PEDs each year [1]. Variable adherence to resuscitation algorithms is commonly observed and can hinder optimal trauma and CPR care, thus jeopardizing patient outcome and survival [60–64]. In addition to the technical skills of individual rescuers, shared mental non-technical skills at the team level such as SA, collective team interaction patterns, leadership, and dynamic decision-making affect adherence to algorithms and hence the outcome of resuscitation care [22, 65].

As a result, new resuscitation strategies relying on information technologies and devices aiming at improving non-technical skills and ensuring adherence to resuscitation guidelines at the team level are of interest. A previous pilot study observed better teamwork and communication using a situation display during simulated resuscitation scenarios [25]. However, there were no overall differences in SA scores between scenarios with and without the situation display as measured by the SAGAT. While the study was not a randomized controlled trial, it provided encouraging results regarding the impact of technology-based cognitive aids in achieving better non-technical skills among emergency department teams in the resuscitation event. In another study, Fitzgerald et al. found that a computer-aided decision support for experienced trauma teams on a large display resulted in improved protocol compliance and a significant reduction in error rates [66]. Unfortunately, the authors did not assess non-technical skills, which is of main interest to our study. Moreover, few studies have investigated the relationship between technical and non-technical skills on CPR performance [12, 67]. Our trial aims to address these flaws by measuring both technical and non-technical skills at the individual and team levels with a cluster randomized controlled trial approach during highly standardized simulation-based resuscitation scenarios.

Our study has some limitations. First, it will be conducted during a resuscitation simulation-based scenario, rather than tested in real-life situations. However, high-fidelity simulation is an essential investigative methodology to answer research questions that cannot be otherwise answered during real CPR as the diversity of patients and their diseases make such studies hard to standardize in critical situations [43]. Given that most results obtained from simulation-based resuscitation studies agree with those obtained from studies in real life, we are confident that InterFACE could be of great interest for real-life situations. Second, standardizing the scenario and the environment will help to avoid effect modifiers by limiting the influence of undesired variables on the outcomes. Third, the 15-min app training will be dispensed just prior to the scenario. In real life, the interval between training and actual use would probably be months. However, training with the app months before the study would unblind participants to its purpose and create a preparation bias. Finally, the Likert-type questionnaire that will be used to measure both perceived stress and satisfaction has not been assessed for validity, internal consistency, reliability, or generalizability. Although it cannot objectively measure these variables, it can be used to measure the difference of perceived stress and satisfaction.

To the best of our knowledge, InterFACE is the first shared decision-making mHealth tool aiming to improve team SA, communication, task performance, and leadership in real-time during in-hospital pediatric trauma and CPR. Importantly, such a digital tool has the potential to enhance adherence to PALS and ATLS algorithms and hence the outcome of resuscitation care. As research in this area is scarce, a study assessing its impact in a simulated environment is warranted before being able to assess it in real life-threatening situations in the vulnerable pediatric population.

## Trial status

The protocol version is 1.0 (13 March 2020). The trial has a declaration of no objection by Swissethics (Req-2020-00294). The trial is registered at ClinicalTrials.gov, ID: NCT04464603, 8 July 2020, https://clinicaltrials.gov/ct2/show/NCT04464603. The recruitment of subjects is expected to start late 2020. We anticipate that the intervention will be completed in early 2021 and study results will be available in mid 2021 (publication expected in mid-2021).

## Data Availability

The final datasets established and analyzed will not be publicly available. An anonymous copy of the final datasets underlying publications resulting from this study will be available from the corresponding author upon reasonable and approved request.

## Abbreviations

AHA: American Heart Association
ATLS: Advanced trauma life support
CA: Cardiac arrest
CI: Confidence interval
CONSORT: Consolidated standards of reporting trials
CPR: Cardiopulmonary resuscitation
GDTA: Goal-directed task analysis
InterFACE: Interconnected and focused mobile apps on patients’ care environment
LCD: Liquid crystal display
N/A: Not applicable
PALS: Pediatric advanced life support
PED: Pediatric emergency department
PedAMINES: Pediatric accurate medication in emergency situations
p-IHCA: Pediatric in-hospital cardiac arrest
p-OHCA: Pediatric out-of-hospital cardiac arrest
ROSC: Return of spontaneous circulation
RTLE: Resuscitation team leader evaluation
SA: Situational awareness
SD: Standard deviation
SPIRIT: Standard Protocol Items: Recommendations for Interventional Trials
SUS: System usability scale
TEAM: Team emergency assessment measure
(T)SAGAT: (Team) situational awareness global assessment technique
pVT: Pulseless ventricular tachycardia
